### Handheld OCT image acquisition and analysis

A non-contact, spectral domain handheld OCT scanner (Envisu C-2300, 3.3 µm axial resolution; Leica Microsystems, Wetzlar, Germany) will be used to scan the ONH and fovea. A 12×8 mm scanning window will be used in the acquisition protocol—this permits imaging of both the ONH and fovea in one scan. The three-dimensional raster scan for both scan sequences will consist of 100 B-scans and 500 A-scans per B-scan line resulting in a short acquisition time (1.9 s) enabling imaging of the ONH and fovea with minimal movement artefact. Handheld OCT will be performed at the time of 48-hour ICP monitoring to fulfil our primary objective; wherever possible, handheld OCT will also be performed during clinic visits to fulfil our secondary objectives. In awake children, visual devices including cartoons on smartphones and tablets will be used as appropriate. Where possible, an assistant can operate the controls to acquire images, otherwise the lead investigator ([name]) will acquire images alone using the foot pedal.

Our imaging protocol involves scanning the right eye followed by the left eye. Once the image is acquired, the en face view is used to identify the ONH, which is navigated frame by frame until the central slice featuring the deepest optic cup is identified for ONH analysis. For foveal segmentation, the fovea is navigated frame by frame until the central slice featuring the deepest foveal pit is identified. Scans are repeated twice per eye where possible, and any scans of non-analysable quality are discarded. Analysable quality is defined as an ONH tomogram wherein the edges of the disc margins and the cup profile, including its lowermost point, can be clearly visualised, or a foveal tomogram wherein it is possible to identify the foveal pit in full and all foveal layers from the external limiting membrane to Bruch’s membrane. In cases of papilloedema, the handheld OCT probe can be repositioned slightly forwards in the axial plane, or the reference arm can be lowered, until the entire swollen ONH is visualised without missing the disc margins. Using this technique, all cases with papilloedema were successfully imaged in our recent feasibility and repeatability study.^47^

ImageJ V.1.48 (National Institutes of Health, Bethesda, Maryland)^48^ shall be used for quantitative segmentation and the ABSnake plugin^49^ shall be used identify the internal limiting membrane contour, which can be corrected manually where required. Lateral distance measurements (defined for adults on the machine) shall be corrected to account for the smaller axial lengths in children using a conversion table according to age from the data presented by Maldonado *et al*.^50^ Optic nerve and retinal analyses will be based on single B-scans through the deepest part of the optic cup and foveal pit, respectively.

Cup and disc parameters will include the following:

Cup depth.Cup width.Cup area.Disc width.

Lateral measurements will be expressed as visual angles rather than distances since disc and cup diameters remain relatively constant in the developing eye or with changing axial length.^37^

Rim parameters will include the following:

Rim width.Rim height (nasal/temporal).Rim area.Nasal and temporal ppRNFL thickness.Total retinal thickness.Bruch’s membrane opening-minimum rim width (nasal/temporal).Bruch’s membrane orientation.Full peripapillary volumetric analysis can be performed wherever possible, using a recently published protocol.^51^

Where available, retinal parameters will include the following:

Macular and perimacular retinal thickness.Foveal pit width.Foveal pit depth.Foveal pit area.Segmentation of all retinal layers.

### ICP assessment

As per standard clinical care at GOSH, patients are admitted for gold-standard, 48-hour ICP assessments. An intraparenchymal catheter and bolt system is used (RAUMEDIC Neurovent-P, RAUMEDIC AG, Helmbrechts, Germany). The neurosurgeon measuring ICP will be masked to the OCT findings. Due to lack of agreement over what ICP values constitute IH in children, two definitions will be used for IH:

Definition 1: Grand mean ICP >15 mmHg, or ICP traces with >2 ICP spikes at least double the baseline ICP and >15 mm Hg for >5 min.Definition 2: Grand mean ICP >20 mmHg, or ICP traces with >2 ICP spikes at least double the baseline ICP and >20 mm Hg for >5 min.

ICP assessments using both definitions will be included in multilevel statistical analyses.

### Secondary outcome data assessment

Fundoscopic examination of the optic discs will be performed by experienced paediatric ophthalmologists and will be graded as follows: normal, papilloedema, mild pallor, severe pallor. Chart logMAR VA will be measured wherever possible using the Thomson Test Chart (Thomson Software Solutions, Hatfield, UK), which uses crowded letter optotypes. If the child is unable to take part in the Thomson Test Chart, then the Keeler logMAR picture test (Keeler, Windsor, UK) will be used . This test requires the child to match easily recognisable pictures (eg, house, car, apple) and is indicated in verbal children who cannot match letter optotypes.^52^ In preverbal children, we will use Keeler Acuity Cards (Keeler) for preferential looking testing. Contrast sensitivity will be measured where possible using the Thomson Test Chart contrast sensitivity module (Thomson Software Solutions, Hatfield, UK), similar to the Pelli-Robson test. Visual field testing will be performed where possible using the Octopus 900 (Haag Streit UK Ltd, Harlow, UK) and/or Humphrey Field Analyzer 3 (Carl Zeiss Ltd, Cambridge, UK). Wherever possible, VEP assessments will be performed and graded according to a modified criterion created by Thompson *et al*.^53^ In children with craniosynostosis monitored at GOSH, clinical assessments and VEPs are currently performed according to an ophthalmological surveillance protocol.^54^

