### Measuring ICP

Measuring ICP in children presents a number of challenges. The gold standard method is direct intraparenchymal measurement, but this involves hospital admission and carries significant risks including infection, bleeding, cerebrospinal fluid (CSF) leak, mechanical failure and general anaesthesia risks.^15^ Another limitation of intraparenchymal measurement is the difficulty in obtaining repeated measures over time. Furthermore, there is no clinical consensus on timing, frequency and duration for accurate measurement, or what figure constitutes raised ICP in children. Many consider ICP greater than 15 mm Hg to be elevated,^2 16–24^ but Hayward *et al*^25^ argue this could reasonably be raised to 20 mm Hg.^25^ Overnight ICP monitoring during natural sleep, which provides a ‘grand average’ with description of the dynamics of the ICP, is considered the gold standard.^26^ In Great Ormond Street Hospital for Children (GOSH), London, monitoring is performed using an ICP bolt (Raumedic AG, Helmbrechts, Germany) for 48 hours according to clinical discretion, particularly in children with clinical suspicion of IH where ophthalmological findings, including fundoscopic and electrodiagnostic findings, are equivocal. This represents an important patient cohort where a more sensitive non-invasive measure could improve clinical decision-making and reduce the need for invasive ICP bolt monitoring. However, the youngest in this group undergoing ICP bolt monitoring are typically toddlers and older, whereas those aged under 1 year with conditions such as craniosynostosis typically undergo surgical treatment expectantly rather than having ICP bolt monitoring.

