### Outcome measures

Our primary outcome measures are OCT examinations and ICP assessments. Our primary OCT outcome measure is retinal nerve fibre layer (RNFL) thickness; other OCT parameters are listed below. OCT examination must be performed at the time of ICP assessment, or within 28 days prior to or 14 days following ICP assessment. Only one visit per child for OCT examination is required to fulfil the primary objective.

Our secondary outcome measures include the following, where possible:

Success rates of handheld OCT in children at risk of IH, particularly in craniosynostosis.Repeated OCT data between clinic visits±ICP assessments±cranial vault expansion surgery±follow up, with repeated ICP data if available.Fundoscopic examination within 3 months of OCT examination and/or at most recent follow-up visit.VA measured within 3 months of OCT examination and/or at most recent follow-up visit.Contrast sensitivity measured within 3 months of OCT examination and/or at most recent follow-up visit.Visual field testing within 3 months of OCT examination and/or at most recent follow-up visit.Visual evoked potentials (VEPs) within 3 months of OCT examination and/or at most recent follow-up visit.Comparison of the above measures with ICP and final VA, where available and appropriate.

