### Sample size calculation

A cohort of at least 39 children is required to demonstrate at least 40% improvement in sensitivity compared with 22% by fundoscopy demonstrated by Tuite *et al*^27^ (McNemar’s Z-test: n=39; power=80%, α=0.05). This would demonstrate sensitivity of at least 62%, a conservative estimate comparable to the least sensitive OCT measure demonstrated by Swanson *et al*^16^ (maximal retinal thickness, 63% sensitivity) for detecting IH in children with craniosynostosis.

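### The fundoscopy grade is not tied in time to the ICP assessment, so the OCT-versus-fundoscopy comparison behind the sample size is open to bias in either direction

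*Protocol article*

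**What the plan says.** All references are to the protocol article.

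- **Sample size calculation.** The target is "at least 40% improvement in sensitivity compared with 22% by fundoscopy demonstrated by" an earlier study, by McNemar's Z-test ("n=39; power=80%, α=0.05"). The text adds: "This would demonstrate sensitivity of at least 62%, a conservative estimate".
- **Outcome measures.** OCT for the primary objective must be done at the ICP assessment, or at most 28 days before or 14 days after it. Fundoscopy is a secondary outcome, accepted as "Fundoscopic examination within 3 months of OCT examination and/or at most recent follow-up visit". The same section plans to compare the secondary measures with ICP where available.
- **Secondary outcome data assessment.** "Fundoscopic examination of the optic discs will be performed by experienced paediatric ophthalmologists", on a four-category scale (normal, papilloedema, mild pallor, severe pallor). Masking is not mentioned.
- **ICP assessment.** This holds the only masking statement in the article: "The neurosurgeon measuring ICP will be masked to the OCT findings".
- **Measuring ICP.** Bolt monitoring is used particularly in suspected IH "where ophthalmological findings, including fundoscopic and electrodiagnostic findings, are equivocal".
- **Handheld OCT image acquisition and analysis.** The inner retinal contour is found by software and may be corrected by hand.
- **Statistical analysis.** Accuracy measures are named for OCT parameters; no OCT-versus-fundoscopy test is named.

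**The concern.** McNemar's test is paired, so the sizing implies that each child has both an OCT result and a fundoscopy grade, each judged against the same ICP label. One of these tests has a tight window around the reference standard. The other has a window that never refers to it, and whose and/or wording leaves open which examination counts.

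A fundoscopy grade made after bolt monitoring differs from one made before it in two ways. The grader may know the ICP or OCT result, and the disc may have changed, especially if treatment came in between. Fundoscopy is a categorical clinical judgement, and the article describes the bolt-monitored group as one where eye findings are often unclear, so there is room for a known result to sway the grade.

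At stake is how the gain in sensitivity is read. If the grades come from a mixture of times before and after ICP, the observed difference between the two tests blends accuracy with timing and knowledge of the result.

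**Working it through.** **Step 1: timing.** Put the ICP assessment at day 0. OCT is allowed from day −28 to day +14. Fundoscopy is allowed within 3 months of OCT, and/or at the most recent follow-up. With OCT at day 0, a grade up to 3 months after ICP qualifies; with OCT at day +14, up to 3 months and 14 days. The follow-up alternative has no upper limit. No wording requires the grade to precede ICP, OCT or treatment.

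**Step 2: reproduce the plan's n.** Let p10 be the proportion of IH-positive children positive on OCT only and p01 the proportion positive on fundoscopy only, with s = p10 + p01 and d = p10 − p01. The normal-approximation formula is

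n = [1.96·√s + 0.842·√(s − d²)]² / d².

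The article does not state the overlap between the tests. With none, p10 = 0.62, p01 = 0.22, s = 0.84, d = 0.40:

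n = (1.796 + 0.694)² / 0.16 = 38.8, rounded up to 39.

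The stated figure is reproduced with a two-sided α of 0.05 and no overlap. Independent results would give 25.3, and nested results (OCT detects every fundoscopy-positive child) 17.1. The figure of 39 is not in dispute.

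**Step 3: illustrate grading towards a known ICP result.** Assumptions, none from the documents: 39 IH-positive children, OCT sensitivity held at 62%, true fundoscopy sensitivity 22%, and a fraction u of fundoscopy-negative IH children upgraded.

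Apparent fundoscopy sensitivity = 0.22 + 0.78u.

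Power = Φ{[d·√39 − 1.96·√s] / √(s − d²)}.

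Example, u = 0.10, no overlap: sensitivity 0.298, d = 0.322, s = 0.918. Power = Φ[(2.011 − 1.878)/0.902] = Φ(0.147) = 56%.

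| u | Apparent fundoscopy sensitivity | Gain (points) | Power, minimum overlap | Power, independent | Power, nested |
|---|---|---|---|---|---|
| 0 | 22% | 40 | 80% | 95% | >99% |
| 10% | 30% | 32 | 56% | 80% | 97% |
| 20% | 38% | 24 | 33% | 56% | 90% |
| 30% | 45% | 17 | 19% | 30% | 74% |

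At u = 30% the sensitivities sum to 0.454 + 0.62 = 1.074, so zero overlap is impossible and the minimum of 0.074 is used.

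**Step 4: the opposite direction.** If late examinations miss resolved papilloedema and apparent fundoscopy sensitivity falls to 15% (also an assumption), the gain becomes 62 − 15 = 47 points. With no overlap, power at n = 39 rises to about 95% and the required n drops to about 25. The gain for OCT would then be overstated.

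**The case against.** The strongest reply is that much of this rests on silence. The article condenses a fuller protocol, and the absence of a masking statement for the fundoscopist does not show that grading is unmasked. That stands, and the point does not depend on it: the fundoscopy window is a rule the article states, and it allows a grade after ICP.

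A second reply is that fundoscopy is only a secondary outcome, the 22% is a literature value that in-study grading cannot change, the window wording is shared with the other visual measures, and Statistical analysis names no test against fundoscopy. All true. But the study is sized by a paired test, and the article plans to compare fundoscopy with ICP; any such comparison would draw on grades admitted by this window.

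A reader might infer that the bias must favour fundoscopy and understate the gain for OCT. The documents do not support that. Late follow-up after treatment can lower fundoscopy sensitivity, as can selecting children with equivocal discs for bolt monitoring. OCT may be done up to 14 days after ICP and its contours corrected by hand, with no stated masking to ICP, which could inflate OCT instead.

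A reader might also infer that the ICP label is seriously exposed because the neurosurgeon is masked only to OCT. That route is narrow: the grand mean and spike thresholds are numeric, and mainly the undefined baseline leaves room for judgement. A label drawn towards visible papilloedema could also raise agreement with OCT of the same disc.

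Finally, the upgrade rates are assumed, and the minimum-overlap column is the most pessimistic. Both tests examine the same disc, so the nested column belongs beside it.

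**Conclusion.** The point holds as a defect of timing. The article sizes the study on a paired comparison with fundoscopy but admits fundoscopy grades made after the ICP and OCT results, and possibly after treatment, while holding OCT close to ICP. The comparison is open to bias in either direction, and the documents settle neither sign nor size.

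The power figures show only how strongly the comparison depends on the comparator's rate. At an assumed 20% upgrading, power is 33%, 56% or 90%, according to overlap. They also take all 39 children as IH-positive, whereas the article says "A cohort of at least 39 children is required". The change is worth making because it closes the timing route in both directions at little cost.

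**What to change.** In Outcome measures, add that for any accuracy comparison using fundoscopy, the grade is the one recorded at the last examination before bolt insertion and before the OCT result is seen. Keep later examinations for the longitudinal outcomes only.

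Two secondary additions would complete the masking: apply Definitions 1 and 2 to the stored ICP trace without reference to the eye findings, and correct OCT contours without knowledge of the ICP result.

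The cost is a sentence in each section concerned and a fixed procedure for labelling the ICP trace. Since the article says the decision to monitor draws on fundoscopic findings, a pre-bolt grade should already exist for many of these children. The few without one drop out of the paired comparison, and their number should be reported.

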### Sample size calculation

A cohort of at least 39 children is required to demonstrate at least 40% improvement in sensitivity compared with 22% by fundoscopy demonstrated by Tuite *et al*^27^ (McNemar’s Z-test: n=39; power=80%, α=0.05). This would demonstrate sensitivity of at least 62%, a conservative estimate comparable to the least sensitive OCT measure demonstrated by Swanson *et al*^16^ (maximal retinal thickness, 63% sensitivity) for detecting IH in children with craniosynostosis.

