**Trial registration number:**

ISRCTN52858719

Strengths and limitations of this studyThis the first diagnostic accuracy study protocol using handheld optical coherence tomography (OCT) to detect intracranial hypertension in at risk children.This protocol promotes transparency of our methodology and reduces the risk of duplication.Fully automated handheld OCT image analysis is not currently available and manual segmentation takes longer, although our evidence-based methodology features semiautomated segmentation.Although handheld OCT can provide in vivo imaging in infants without sedation, it could be especially challenging in this patient population, which could limit imaging success rates.Gold standard intracranial pressure measurements form our reference standard, but these are only performed in select patients, thus limiting our overall recruitment.

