The ideal measure of ICP would be non-invasive, acceptable for children, quantitative and would permit serial measurements to appreciate evolving changes related to rising ICP. Existing surrogate measures of ICP do not fulfil all these criteria, including fundoscopy,^27^ radiography^28^ and ocular ultrasonography,^29^ each failing to provide adequate sensitivity to be used as screening tools. In particular, funduscopy is routinely used in paediatric ophthalmology clinics to detect IH. Tuite *et al*^27^ demonstrated that fundoscopy yielded sensitivity of only 22% for IH in children with craniosynostosis aged under 8 years old, while specificity was 98%. Hence, papilloedema detected on fundoscopy reliably indicates IH in younger children with craniosynostosis, but crucially its absence does not exclude IH.

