### Handheld OCT

OCT has revolutionised the clinical practice of ophthalmology over the past two decades. However, infants and young children have previously been largely deprived of this technology as conventional OCT machines were designed for adults, requiring compliance with a chin rest, good fixation and cooperation. These limitations have been overcome with the recent advent of the handheld spectral-domain OCT designed for infants, which is demonstrably reliable in awake infants.^30 36^ Normal development of the optic nerve^37^ and retina^38^ in children has recently been described using handheld OCT. A wide range of conditions have also been investigated using handheld OCT in children, including retinopathy of prematurity,^39^ nystagmus,^40^ foveal hypoplasia,^41^ optic nerve hypoplasia,^41^ achromatopsia,^42^ albinism,^43^ primary congenital glaucoma,^44^ microcephaly,^45^ craniopagus twins^46^ and others.

More recently, we performed a feasibility and repeatability study^47^ using handheld OCT in children with craniosynostosis (n=50, median age 51 months, age range 2–157 months). We found good feasibility, with 86% achieving at least unilateral OCT and 76% achieving bilateral OCTs of the ONH. This was higher than the success rate in healthy children found by Patel *et al*^37^ (70% achieving at least unilateral OCT imaging of the ONH). Factors boosting the likelihood of success in children with craniosynostosis included good understanding and cooperation of the child and parent/guardian and availability of an assistant. We also performed repeatability analysis in 20 children and found good repeatability (intraclass correlation coefficient range, 0.77–0.99; the majority exceeded 0.90).

Advantages of using handheld OCT in children at risk of IH include the following:

Handheld OCT can be performed in awake babies and infants, without the need for general anaesthesia.Even if under general anaesthesia, handheld OCT can be performed in a child lying down, both in the supine and lateral decubitus positions.Handheld OCT scans can be easily repeated in the clinical setting, enabling the assessment of evolving changes over time.Handheld OCT semiautomated segmentation parameters can be fully controlled by the investigator.^37 38 47^

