### Inclusion criteria

Patients aged 0–18.Clinical and/or genetic diagnosis of craniosynostosis, IIH, space occupying lesion or other conditions association with IH.

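### The sample size of 39 counts IH-positive children with paired test results, but the protocol gives it as the size of the cohort

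*Protocol article*

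**What the plan says.** The only sample size justification is in the Sample size calculation section of the protocol article: "A cohort of at least 39 children is required to demonstrate at least 40% improvement in sensitivity compared with 22% by fundoscopy". The method is given as "McNemar’s Z-test: n=39; power=80%, α=0.05". The target follows: "This would demonstrate sensitivity of at least 62%, a conservative estimate comparable to the least sensitive OCT measure". The 40% improvement is therefore 40 percentage points, from 22% to 62%. The comparator comes from a published craniosynostosis series described under Measuring ICP, where "fundoscopy yielded sensitivity of only 22% for IH in children with craniosynostosis aged under 8 years old, while specificity was 98"%.

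The section gives no IH prevalence, no number of IH-positive children, no discordance between the tests, and no allowance for scans that cannot be analysed.

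Elsewhere the article describes who will be studied:

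- Inclusion criteria: "Clinical and/or genetic diagnosis of craniosynostosis, IIH, space occupying lesion or other conditions association with IH". This is a population at risk of IH, not one with confirmed IH.
- Measuring ICP: bolt monitoring is used "particularly in children with clinical suspicion of IH where ophthalmological findings, including fundoscopic and electrodiagnostic findings, are equivocal". IH status is therefore unknown when the child is monitored.
- ICP assessment: IH is defined in two ways, with cut-offs of 15 and 20 mm Hg.
- Statistical analysis: specificity and both predictive values are planned alongside sensitivity.
- Handheld OCT: imaging success in the earlier craniosynostosis feasibility study is reported, "with 86% achieving at least unilateral OCT and 76% achieving bilateral OCTs of the ONH".

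**The concern.** Sensitivity is a proportion among children who have the condition. A paired comparison of two sensitivities draws its information only from IH-positive children with both an OCT and a fundoscopy result. IH-negative children inform specificity and add nothing to this test. If the McNemar formula returns 39, all 39 must be IH-positive and evaluable on both tests. The protocol attaches that number to the cohort.

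A cohort of 39 cannot supply 39 IH-positive children and also the IH-negative children needed for the planned specificity. If the team treats 39 monitored children as enough, the primary objective may be analysed with well under the advertised power and a wide interval for sensitivity. The article already says that ICP-monitored children are scarce ("Gold standard intracranial pressure measurements form our reference standard, but these are only performed in select patients, thus limiting our overall recruitment"), so it matters which children the target counts.

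**Working it through.** **Inputs.** Sensitivities 0.22 and 0.62, difference d = 0.40, alpha 0.05, power 80% (all from Sample size calculation). Sidedness is not stated; two-sided is used because it reproduces 39. Discordance (psi) and IH prevalence are not stated, so both are varied below.

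**Step 1: reproduce 39.** For the paired McNemar Z-test,

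n = [1.960 × √psi + 0.842 × √(psi − d²)]² / d²

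The largest psi compatible with these sensitivities is 0.62 + 0.22 = 0.84, when no IH-positive child is positive on both tests:

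n = [1.960 × √0.84 + 0.842 × √(0.84 − 0.16)]² / 0.16 = (1.796 + 0.694)² / 0.16 = 38.76, rounded up to **39**.

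Full enumeration of the uncorrected test at 39 pairs gives 81% power. The figure is right as a count of IH-positive pairs. No prevalence term enters it.

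**Step 2: other discordances.**

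- Independent given IH: psi = 0.22 × 0.38 + 0.62 × 0.78 = 0.0836 + 0.4836 = 0.567. Then n = (1.476 + 0.537)² / 0.16 = 25.3, so **26**.
- Minimum (OCT finds every case that fundoscopy finds): psi = 0.40. Then n = (1.240 + 0.412)² / 0.16 = 17.05, so **18**.

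Of these three cases only the maximum gives 39. One-sided testing at psi = 0.84 gives 31.

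**Step 3: power if 39 children are monitored and all are imaged.** IH-positive count = 39 × prevalence, rounded. Power is for the uncorrected two-sided test, by enumeration.

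| Assumed prevalence | IH-positive | psi 0.84 | psi 0.567 | psi 0.40 |
|---|---|---|---|---|
| 40% | 16 | 40% | 59% | 94% |
| 50% | 20 | 52% | 70% | 98% |
| 70% | 27 | 66% | 85% | over 99% |
| 80% | 31 | 72% | 90% | over 99% |
| 100% | 39 | 81% | 96% | over 99% |

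The uncorrected test is liberal when discordant pairs are few. At psi = 0.40, the exact test gives 67% with 16 pairs and 87% with 20.

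**Step 4: children needed for 39 IH-positive.** With all imaged: 39/0.40 = 97.5, so 98; 39/0.50 = 78; 39/0.70 = 55.7, so 56; 39/0.80 = 48.75, so 49. If the 86% imaging success also applied: 39/(0.40 × 0.86) = 113.4, so **114**; 39/(0.50 × 0.86) = 90.7, so **91**.

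**Step 5: precision.** If 12 of 20 IH-positive children were detected (60%), the Wilson 95% interval has centre (0.60 + 3.84/40) / (1 + 3.84/20) = 0.584 and half-width 1.96 × √(0.24/20 + 3.84/1600) / 1.192 = 0.197, so it runs from about 39% to 78%.

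**The case against.** The strongest reply is that the size of the shortfall cannot be read from the document, and much of it stands.

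- **Discordance.** A psi of 0.84 requires OCT to miss every child whose papilloedema fundoscopy detects. Both tests look at the optic disc, and the article reports that all papilloedema cases were imaged in the feasibility study, so positive agreement is more plausible. Under independence, 26 IH-positive children suffice, and 39 monitored children would be enough at a prevalence of about 26/39 = 67%. At the minimum discordance, 18/39 = 46% would do. A reader might infer that the study is certain to be underpowered. The documents do not support that; the failure is of the 80% claim on the inputs that yield 39.
- **Prevalence.** Children are selected for monitoring on clinical suspicion, and spike patterns also count as IH, so prevalence may be well above 50%. Any single figure for the IH-positive count is an assumption.
- **Imaging loss.** The 86% comes from a craniosynostosis sample aged 2 to 157 months. Bolt-monitored children are typically toddlers or older, and scans can also be taken under general anaesthesia. A 14% loss is one scenario, not an expected fact.
- **Children without ICP data.** A reader might count these as a further loss, because the inclusion criteria do not require monitoring. Outcome measures and the image acquisition section tie the primary objective to OCT around the ICP assessment, so 39 can fairly be read as monitored children.
- **A floor, not a stopping rule.** The protocol says at least 39 and plans to run to February 2024. Recruitment may go further, but the floor is still presented as sufficient.

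None of this changes the unit. Even among monitored children, 39 is the number who must be IH-positive. An analysis plan or fuller protocol could add detail, but could not make 39 monitored children equal 39 IH-positive ones.

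**Conclusion.** The point holds in this form: 39 is a correct count of IH-positive children with an analysable OCT and a paired fundoscopy, and it is wrongly worded as the size of the cohort. The arithmetic is sound; it is applied to the wrong population. On the implied inputs (two-sided alpha 0.05, discordance 0.84), power falls below 80% once the cohort includes more than a child or two without IH, and the protocol's own selection criteria and planned specificity show that it will include such children.

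The size rests on two assumptions that the protocol does not supply. Across prevalence of 40% to 80% with complete imaging, power ranges from about 40% to 72% at the implied discordance and from about 59% to 90% under independence. At minimum discordance it may be adequate. The IH-positive count also depends on the definition: any child who meets the 20 mm Hg definition meets the 15 mm Hg one, so the count under the higher cut-off can only be equal or smaller. No single corrected total can be derived from the document.

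**What to change.** In Sample size calculation:

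1. Restate 39 as the number of children who are IH-positive under one named definition and have an analysable OCT and a paired fundoscopy.
2. State the assumed discordance and the sidedness of alpha. If a discordance below 0.84 can be justified, recalculate the IH-positive number from it.
3. Give the implied number of ICP-monitored children over a range of prevalence and imaging success. For 39 IH-positive children this is 98 at 40% prevalence and 78 at 50% with complete imaging, or 114 and 91 at 86% imaging success.
4. If recruitment will stay near 39 monitored children, replace 80% with the power and confidence interval width that the expected IH-positive count gives.

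The cost is a change of wording and a short table. No procedure, endpoint or analysis has to change. The stated power becomes less favourable if the cohort is not enlarged; enlarging it would take more monitored children, whom the article describes as limited in number.

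### The sample size of 39 rests on an undeclared zero-overlap McNemar assumption, holds only if it counts IH-positive children, and cannot demonstrate a sensitivity of at least 62%

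*Protocol article*

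**What the plan says.** The Sample size calculation states that "A cohort of at least 39 children is required" to show "at least 40% improvement in sensitivity compared with 22% by fundoscopy", the 22% being taken from a published fundoscopy study. The method is given as McNemar's "Z-test: n=39; power=80%, α=0.05". The section then concludes: "This would demonstrate sensitivity of at least 62" per cent, and describes this as a conservative figure by comparison with the least sensitive OCT measure in another cited study ("maximal retinal thickness, 63% sensitivity").

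The section gives no discordant proportions, no overlap between OCT and fundoscopy, no sidedness and no expected proportion of children with IH. The Subjects and Inclusion criteria sections define the cohort as children with conditions associated with IH, not children shown to have it. Under Outcome measures the paired comparator is a secondary outcome, collected where possible: "Fundoscopic examination within 3 months of OCT examination and/or at most recent follow-up visit".

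**The concern.** McNemar's test uses only the children on whom the two tests disagree. Its sample size therefore depends on the two discordant proportions, and two marginal sensitivities do not fix these until the overlap is stated. A single n quoted from 22% and 62% alone hides an assumption.

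Three things follow. The reader cannot tell what 39 assumes. Sensitivity is defined only in children with IH, so 39 at-risk children and 39 IH-positive children carry different power. And the conclusion about 62% turns the design's assumed true value into something a significant result would prove, for a test that the introduction hopes will reduce the need for invasive monitoring.

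**Working it through.** **Inputs** (Sample size calculation): fundoscopy sensitivity 0.22; gain 0.40, which must be in absolute points because 0.22 + 0.40 = 0.62; power 80%; α = 0.05. Sidedness is not stated; I take two-sided.

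**Formula.** Let p10 be the proportion of IH-positive children found by OCT only, p01 by fundoscopy only and p11 by both. Let s = p10 + p01 and d = p10 − p01 = 0.40. For McNemar's Z-test,

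n = [1.96·√s + 0.8416·√(s − d²)]² / d².

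**1. Reproducing 39.** Enter p10 = 0.62 and p01 = 0.22, so s = 0.84 and s − d² = 0.68:

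n = (1.796 + 0.694)² / 0.16 = 38.76, rounded up to **39**.

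If the sensitivities are 0.62 and 0.22, these cells force p11 = 0.62 − 0.62 = 0: OCT misses every case that fundoscopy finds.

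**2. The same figures as marginal sensitivities.** Here p10 = 0.62 − p11 and p01 = 0.22 − p11.

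| Overlap | p11 | p10 | p01 | s | n | IH-positive pairs |
|---|---|---|---|---|---|---|
| None | 0 | 0.62 | 0.22 | 0.84 | 38.76 | 39 |
| Half of fundoscopy positives | 0.11 | 0.51 | 0.11 | 0.62 | 27.93 | 28 |
| Independence | 0.1364 | 0.4836 | 0.0836 | 0.5672 | 25.33 | 26 |
| Full (OCT finds all fundoscopy positives) | 0.22 | 0.40 | 0 | 0.40 | 17.05 | 18 |

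Other routes do not give 39: one-sided at s = 0.84 gives 30.3; two independent groups, 23 per group; a one-sample test against 22%, 10; a relative 40% gain, 87 to 533. A continuity correction gives 41.2 at zero overlap and about 39 at p11 = 0.02, so the implied overlap is still close to nil.

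**3. Power by number of IH-positive pairs, m.** Power = Φ{[d√m − 1.96√s] / √(s − d²)}. The protocol gives no prevalence of IH, so the 50% and 30% rows are assumptions.

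| IH-positive pairs | Zero overlap | Independence | Full overlap |
|---|---|---|---|
| 39 (all have IH) | 80.3% | 94.5% | 99.5% |
| 20 (50% have IH) | 50% | 69% | 87% |
| 12 (30% have IH) | 31% | 44% | 62% |

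Example, m = 20 at independence: (0.4·4.472 − 1.476) / 0.638 = 0.49, and Φ(0.49) = 0.69.

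**4. The 62% statement.** McNemar's null is a difference of zero. With m = 39 and s = 0.84 the test rejects once the observed difference reaches about 1.96·√(0.84/39) = 0.29, well short of 0.40. If OCT detects 24/39 (61.5%), the 95% CI is 45.9–75.1% (Wilson) or 44.6–76.6% (exact). The lower limit first exceeds 62% at 31/39 (79%). If the true sensitivity is 62%, the chance that the exact lower limit exceeds 62% is about 1.6%.

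**The case against.** The best defence is that the slip, if it is one, lies on the safe side. With these sensitivities, zero overlap gives the most discordance possible (0.84, below 1), so 39 is the largest number the Z-test can require, and 39 IH-positive pairs give at least the stated 80% power under any overlap. That stands. A reader might infer that 39 is too small, or that 26 should replace it; the arithmetic supports neither. The defence fails only where it takes all 39 children to be IH-positive, which the protocol does not say. Nor does the protocol declare zero overlap as a worst case: its word conservative describes the 62%.

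A reader might also infer that zero overlap contradicts the protocol's own report that "all cases with papilloedema were successfully imaged in our recent feasibility and repeatability study". It does not. That sentence concerns obtaining a usable scan, not whether OCT would classify the child as having IH. Zero overlap is implausible, but the text does not refute it.

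The figure might have come from elsewhere, for example 26 inflated for failed imaging. With the 70% success rate quoted for healthy children, 26/0.70 = 37.1, so 38, and the section mentions no inflation. The discordant-cell explanation remains an inference, though the only one found that returns 39 from the printed inputs.

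Finally, the 62% sentence goes on to present the figure as an estimate, and the Statistical analysis section sets no 62% criterion. So no planned analysis changes, but the wording still claims more than the test can show.

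**Conclusion.** The point holds as a fault of specification and wording. The 39 is the zero-overlap worst case of a range of 18 to 39 IH-positive pairs, and the section does not say so. If all 39 are IH-positive with both tests, power is 80% at worst and about 95% under independence. If 39 is the whole at-risk cohort, as written, the stated 80% does not follow: assuming 50% with IH, power is about 50% to 87%; assuming 30%, about 31% to 62%. A reader might conclude that the study is underpowered. The documents do not support that firmly, because they give no prevalence; they show only that the 80% is not secured.

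The claim of demonstrating at least 62% is wrong however n was obtained. The power figures assume a two-sided Z-test without continuity correction, by normal approximation; an exact test at zero overlap would have about 75% power with 39 pairs.

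**What to change.** Rewrite the Sample size calculation paragraph:

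- State the assumed discordant proportions or overlap, give the range of 18 to 39, and keep 39 as the declared worst case. Do not lower the target. State that α is two-sided, if it is.
- State that the figure counts IH-positive children with paired OCT and fundoscopy.
- Give the number of IH-positive children expected in the cohort, with its source, under each of the two IH definitions, and restate the power for that number.
- Replace the 62% sentence with wording such as: power to show OCT sensitivity greater than fundoscopy if the true OCT sensitivity is 62%. Add the expected confidence interval, about 46–75% with 39 IH-positive children.

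The cost is one paragraph, with no change to study procedures. The downside is that the restated power may be less favourable than 80%. If the sponsor then wants 80% power in IH-positive pairs, more children may have to be recruited.
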